### Strategies to improve adherence to interventions {11c}

Principal investigator and co-investigators will explain the whole study protocol and meanings of randomization to the participants before enrollment to make sure they understand and are able to comply with the study schedule. After randomization, study nurses will maintain close contact with participants and ask them to report adverse events and return for examinations and outpatient clinic visits.

### Relevant concomitant care permitted or prohibited during the trial {11d}

Standardized care for patients with GO will be provided in every enrolled subject, including treatment of hyperthyroidism to achieve euthyroidism, refrain from smoking, or use of eyedrops or lubricants for dry eye. During study period, additional use of systemic steroid (oral or intravenous) is prohibited.

### Provisions for post-trial care {30}

Immediate consultation and medical assistance will be provided to participants with suspected adverse events related to HCQ without additional expenses. After trial completion, the patients will be followed regularly by their endocrinologist and ophthalmologist to discuss further treatment strategies for GO.

### Outcomes {12}

Primary endpoint of this study is the composite ophthalmic outcome of ophthalmic examinations including eyelid aperture, soft tissue involvement, and exophthalmos at the 24th week and 48th week of study, with definitions in line with the previous literature for comparison [4]. 

The primary endpoint is a composite ophthalmic outcome assessed at weeks 24 and 48. Based on predefined criteria (as shown in Table 1), participants will be classified as follows:Improvement: achievement of at least one improvement criterion in any domain, without meeting any deterioration criteria in the othersDeterioration: meeting any deterioration criterion in one or more domainsStable: neither improved nor deteriorated in any domain

**Table 1 Tab1:** Definition of the composite ophthalmic outcome (primary endpoint)

Ophthalmic domain	Measure	Result classifications		
		Improvement	Stable	Deterioration
Eyelid aperture	Slit lamp	Decrease by ≥ 2 mm	Neither improved nor deteriorated	–
Soft tissue involvement	NOSPECS class 2 signs	Reduction of ≥ 1 grade in NOSPECS class 2 signs		1. Increase ≥ 1 NOSPECS class 2. New NOSPECS class
Exophthalmos	Hertel exophthalmometer	Decrease by ≥ 2 mm		–
Other ophthalmic signs				Vision acuity deterioration or other evidence of optic nerve compression

NOSPECS is a clinical classification system for assessing the severity of Graves’'orbitopathy [7], consisting of the following seven classes (class 0–6):

Class 0: No signs or symptoms; Class 1: Only signs, no symptoms (e.g., lid retraction); Class 2: Soft tissue involvement (e.g., periorbital edema, conjunctival injection, chemosis); Class 3: Proptosis; Class 4: Extraocular muscle involvement; Class 5: Corneal involvement; Class 6: Sight loss due to optic nerve compression

In this study, improvement or deterioration in soft tissue involvement is assessed based on changes in class 2 severity. Deterioration is defined as a worsening of at least one grade in any NOSPECS class, or the appearance of a new class not previously present Improvement: achievement of at least one improvement criterion in any domain, without meeting any deterioration criteria in the others Deterioration: meeting any deterioration criterion in one or more domains Stable: neither improved nor deteriorated in any domain

Secondary endpoints:Changes in GO-Quality of Life Questionnaire (GO-QoL) scores (visual functioning and appearance subscales) at the 24th week and 48th week: A change of 6 points is considered a minimal clinically important difference (MCID). An increase of 6 points in any category is considered improvement, a decrease of 6 points is considered deterioration, and anything in between is classified as stable [13].Changes in non-contrast orbital CT at the 24th week and 48th week, including the ratio and density differences of muscle volume, fat volume, and orbital volume [14].Diplopia will be assessed at the 24th and 48th weeks using the Gorman score, a validated grading system endorsed by the EUGOGO [15]. This scale classifies diplopia into four categories:0—no diplopia1—intermittent diplopia2—inconstant diplopia3—constant diplopia in the primary position or on readingCAS, measured by the 7-point CAS [16], at the 24th week and 48th week.Visual acuity, assessed using best-corrected visual acuity (BCVA, Snellen chart), at the 24th week and 48th week.Changes in serum inflammatory and fibrosis markers at the 24th week and 48th week.Changes in thyroid antibodies at the 24th week and 48th week.

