### Sample size {14}

The sample size was estimated using Stata software. Due to the lack of literature on the effects of HCQ for mild GO, we referred to the clinical trial published by the NEJM in 2011, which investigated the efficacy of selenium in patients with mild GO [4]. Approximately 12% of GO patients showed spontaneous improvement, and the use of selenium significantly increased this improvement rate to 37% (absolute difference of 25%). We hypothesized that HCQ improves the prognosis of mild GO patients by at least the same proportion as selenium, i.e., 25% of improvement rate [3]. As selenium is now considered a recommended treatment option for mild GO in clinical guidelines, we reasoned that hydroxychloroquine should demonstrate at least comparable efficacy to warrant further investigation. Based on a 2:1 random allocation ratio, a two-sided *α* of 0.05, and 80% power, the estimated sample size was 72 participants in the HCQ group and 36 in the control group.

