### Statistical methods {20a, 20b, 20c}

Basic characteristics will be presented using descriptive statistics, including mean (standard deviation) and number of occurrences (percentage). For non-normally distributed data, the median (interquartile range, IQR) will be used. To compare between the treatment group and the observation group, depending on the nature of the data, Student’s *t*-tests will be used for continuous variables, and chi-square tests or Fisher’s exact tests will be used for categorical variables, to examine the differences between the two groups.

To compare the scores of the GO-QoL and the CAS before and after treatment, two-sided *t*-tests and Mann–Whitney tests will be used. Pearson’s correlation analysis will be utilized to test the association and determine the correlation coefficient (*r*) among variables of interest. The severity of thyroid eye disease before and after treatment in both groups will be compared in terms of the proportion of patients who show improvement, stability, or deterioration. One-way repeated measures analysis of variance (ANOVA) will be used to analyze the change of variables before and after treatment. In addition to ANOVA, ANCOVA and regression models will be used to adjust for baseline differences and estimate effect sizes with confidence intervals.

Exploratory subgroup analyses will be performed to assess whether treatment effects differ by age, gender, baseline TBII levels, duration of GO, and smoking status. These analyses are intended to explore potential effect modifiers and will be interpreted cautiously given the limited sample size. A two-tailed *P* value < 0.05 will be considered statistically significant. Statistical analysis will be performed using Stata/SE 14.0 for Windows (StataCorp, College Station, TX, USA).

All randomized participants, including those who discontinue the intervention prematurely, will be included in the primary analysis based on the intention-to-treat (ITT) principle. Sensitivity analyses will be conducted if necessary to evaluate the robustness of results in the presence of missing data. Missing data will be handled using multiple imputation under the assumption of missing at random (MAR).

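### The composite is declared primary at both week 24 and week 48 with no success rule, while the trial is sized for one comparison at two-sided 0.05

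*Protocol article*

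**What the plan says.** **Outcomes {12}** gives the primary endpoint in two consecutive statements, and both carry two time points. The first lists the three components of the composite and closes with "exophthalmos at the 24th week and 48th week of study, with definitions in line with the previous literature for comparison". The second says "The primary endpoint is a composite ophthalmic outcome assessed at weeks 24 and 48". Neither ranks the weeks or says what pattern of results would count as a positive trial.

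**Study setting {9}** gives six months of HCQ and then six months of observation. Week 24 is therefore about the end of treatment, and week 48 about six months off drug.

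**Statistical methods {20a, 20b, 20c}** says that disease severity in the two groups "will be compared in terms of the proportion of patients who show improvement, stability, or deterioration", without naming a week. For this kind of outcome, "chi-square tests or Fisher’s exact tests will be used for categorical variables". One general threshold follows: "A two-tailed *P* value < 0.05 will be considered statistically significant". No hierarchy, alpha split or joint test of the two weeks is described.

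**Sample size {14}** uses improvement rates of 12% and 37%, 2:1 allocation and "a two-sided *α* of 0.05, and 80% power", from which "the estimated sample size was 72 participants in the HCQ group and 36 in the control group". It does not attach these rates to either week.

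**Interim analyses {21b}** plans none, so no alpha is spent elsewhere.

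**The concern.** The design calculation spends the whole 5% on one comparison, yet the endpoint definition supplies two. The two weeks also ask different things: week 24 asks about effect at the end of treatment, week 48 about persistence after it. A split result is quite possible, and the article gives no rule for reading one.

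At stake is a design property that the article states. If either week can carry the claim, the 0.05 is not held. If both must, the 80% power is not delivered. If one week is meant, the article does not say which, and in an open-label trial that should be fixed before anyone sees results.

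**Working it through.** **Inputs.** From Sample size {14}: 12% and 37%, 2:1 allocation, two-sided 0.05, 80% power, 36 control and 72 HCQ patients. From Outcomes {12}: two primary weeks. Assumed, because the article does not give them: the correlation between the two weeks' results, and the improvement rate shared by both groups under the null.

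**1. Reproducing the stated size.** Pooled-variance formula for two proportions, no continuity correction, n = control group:

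n = [z(0.975)·√(p̄(1−p̄)·1.5) + z(0.80)·√(p1(1−p1) + p2(1−p2)/2)]² / (p2−p1)²

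- p̄ = (0.12 + 2×0.37)/3 = 0.2867
- First term: 1.960 × √(0.2867×0.7133×1.5) = 1.0855
- Second term: 0.8416 × √(0.1056 + 0.1166) = 0.3967
- n = (1.4822/0.25)² = 35.1, rounded up to 36; HCQ 72; total 108

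The stated 72/36 is reproduced as one test at the full two-sided 0.05. Power at 36/72 is 81.0% by this approximation and 82.0% by exact enumeration of the uncorrected chi-square test.

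**2. Either week suffices, each tested at 0.05.** Independent results give 1 − 0.95² = 9.75%. For correlated results the rate is 1 − P(|Z1| < 1.96, |Z2| < 1.96) under a bivariate normal:

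| Correlation | False-positive rate |
|---|---|
| 0 | 9.75% |
| 0.5 | 9.1% |
| 0.7 | 8.3% |
| 0.8 | 7.8% |
| 0.9 | 7.0% |
| 1 | 5.0% |

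**3. The same with binary data.** Simulated uncorrected chi-square tests, 36 against 72 patients, 100,000 trials per setting, with the correlation set between a patient's two outcomes:

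| Null improvement rate | Correlation 0.5 | 0.7 | 0.8 |
|---|---|---|---|
| 12% | 8.0% | 7.4% | 7.0% |
| 25% | 9.5% | 8.7% | 8.2% |
| 37% | 9.3% | 8.6% | 7.9% |

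The 12% row is lower because a single chi-square test is conservative there, with an actual size of about 4.4%. At 25% a single test has an actual size of about 5.2%, and at zero correlation the simulated either-week rate is 10.1%. The 9.75% is therefore the ceiling for tests of exact 5% size, and test discreteness can move it slightly.

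**4. Both weeks must be significant.** The false-positive rate is then well below 5%: about 0.2-2.3% in the same simulations at correlations of 0 to 0.8. With 80% power at each week, joint power is P(Z1 < 0.8416, Z2 < 0.8416): 68.7% at correlation 0.5 and 71.3% at 0.7.

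**5. Splitting alpha at 0.025 per week.** With z = 2.241 in place of 1.960, the first term becomes 1.2414 and n = (1.6381/0.25)² = 42.9, rounded up to 43. That means 86 HCQ patients and 129 in total. At the planned 108, power per week falls to 70.8% by the approximation and 72.2% by exact enumeration.

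**The case against.** Three points can fairly be made for the plan.

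First, the article does not say that two separate tests will be run at 0.05, or that a win at either week is enough. A reader might infer that the trial therefore has a false-positive rate of about 8-9%. The documents do not support that as a fact. It needs an either-week rule, which is not stated, and a correlation of about 0.5-0.8, which is not given. At the protocol's own 12% improvement rate the simulated figure is nearer 7-8%, and if both weeks are required it is below 5%. This part of the objection stands, and every error rate here is conditional.

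Second, multiplicity procedures often sit in a statistical analysis plan, which is not shown. That is fair as regards the procedure, and its absence alone would not be a finding. But the time point is part of the endpoint definition, and this article does not leave it open: it names both weeks as primary beside a one-comparison sample size. An analysis plan could settle this only by narrowing or interpreting what is published here.

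Third, both weeks are declared in advance, so any later choice is between two options only. That limits the harm and is why the error rate stays near or below 10%. It does not bring it to 5%.

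The 69-71% power also has a weak spot. It assumes the same 80% at week 48, six months off drug, and no document gives an effect at that time. If the effect fades after stopping, joint power would be lower.

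**Conclusion.** The point holds in conditional form. Two weeks are labelled primary, no success rule links them, and the sample size supports one comparison at two-sided 0.05.

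- **Either week counts:** the false-positive rate exceeds 5%. It is about 9.75% for independent results, and roughly 7-9.5% at assumed correlations of 0.5-0.8 and null improvement rates of 12-37% (about 7-8% at 12%).
- **Both weeks required:** alpha is controlled, but power is about 69-71%, assuming 80% at each week and correlations of 0.5-0.7.
- **One week intended:** alpha and power are as stated, but the article does not name the week.

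A reader might also infer that the 12% against 37% calculation belongs to week 24. It does not settle that, because Sample size {14} ties those rates to no week.

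This concerns the trial's only primary claim and should be resolved before outcome data are seen. I am confident of the defect, less so of the exact error rate, which depends on inputs the article does not supply.

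**What to change.** In Outcomes {12}, name one week as the single primary time point and make the other a key secondary. Week 24 is a natural choice because it marks the end of treatment, but the choice is the sponsor's. In Statistical methods, add that the second week is tested at 0.05 only if the first is significant. This fixed sequence holds alpha at 0.05 across the two tests and leaves the 72/36 calculation valid for the named week.

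The cost is one sentence in each section, ethics committee approval and a registry update, for which Protocol amendments {25} already provides. No patients are added. The downside is that a claim at the second week becomes conditional on the first.

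If the sponsor prefers to keep both weeks primary, the success rule must be written down with a matching sample size. Either-week success with a 0.025 split needs 129 patients (86/43) for 80% power at each week. Both-week success needs no alpha split, but its power must be recalculated with a stated week-48 effect and correlation.

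### The primary composite is not uniquely defined: its Improvement and Deterioration rules overlap, and Table 1 and its note disagree on what counts as deterioration

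*Protocol article*

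**What the plan says.** Outcomes {12} of the protocol article sets out the primary endpoint as a three-way classification at weeks 24 and 48 and refers to Table 1 for the criteria.

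- To be classed as **improved**, a participant needs "achievement of at least one improvement criterion in any domain, without meeting any deterioration criteria in the others".
- The **deteriorated** label is broader and needs only "meeting any deterioration criterion in one or more domains".
- The **stable** label is left for participants who have "neither improved nor deteriorated in any domain".

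Table 1 has four rows. Eyelid aperture and exophthalmos each have an improvement criterion (a decrease of at least 2 mm) and a dash under deterioration. The soft-tissue row has an improvement criterion, a reduction of at least one "grade in NOSPECS class 2 signs", and two deterioration criteria: an increase of at least one NOSPECS class, or a new class. The fourth row, for other signs, has only a deterioration criterion (visual acuity or optic nerve compression).

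The note under the table first says that "improvement or deterioration in soft tissue involvement is assessed based on changes in class 2 severity". The sentence that follows it is wider in scope and reads: "Deterioration is defined as a worsening of at least one grade in any NOSPECS class, or the appearance of a new class not previously present". The same note lists lid retraction as an example of class 1 and names class 3 as proptosis.

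**The concern.** A three-way endpoint needs categories that are exhaustive and mutually exclusive, and one rule that gives one answer for each set of measurements. Two features of the text prevent this.

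1. Improvement is blocked only by deterioration in the *other* domains, whereas Deterioration is triggered by any domain. A domain that can improve and deteriorate at once therefore produces a double label. The soft-tissue row is such a domain: its improvement criterion looks at class 2 only, while its deterioration criteria reach across the NOSPECS classes.
2. The table and the note give different deterioration rules. The table counts a change of *class* and gives aperture and exophthalmos no deterioration criterion. The note counts a change of *grade* in any class, which brings lid retraction and proptosis back in.

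The improvement rate is the quantity on which the trial is powered. The trial is open-label. Blinded ophthalmologists protect the measurements, but not a later choice between two published scoring rules. That choice should be closed before anyone sees outcomes by arm.

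**Working it through.** **Planning figure.** Inputs from Sample size {14}: improvement 12% (control) and 37% (HCQ), 2:1 allocation, two-sided α 0.05, power 80%. With the pooled-variance formula and no continuity correction:

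- Pooled rate = (0.12 + 2 × 0.37)/3 = 0.2867.
- 1.960 × √(1.5 × 0.2867 × 0.7133) = 1.0855.
- 0.8416 × √(0.12 × 0.88 + 0.37 × 0.63/2) = 0.3967.
- Control n = (1.0855 + 0.3967)² / 0.25² = 35.15, rounded up to 36. HCQ n = 72. Total 108, as stated.

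The sample size reproduces, and it rests wholly on the improvement rate.

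**Overlap within Table 1.** Let aperture and exophthalmos each be improved, unchanged, or up by 2 mm or more (3 states each). Let soft tissue be improved, unchanged, deteriorated, or both (4 states), and other signs be absent or deteriorated (2 states). That gives 3 × 4 × 3 × 2 = 72 patterns. Under Table 1 and the three definitions:

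| Result | Patterns | How they arise |
|---|---|---|
| Deteriorated only | 45 | other signs deteriorated (36), plus soft tissue deteriorated only with no other signs (9) |
| Improved only | 14 | soft tissue improved only (9), plus soft tissue unchanged with aperture or exophthalmos improved (5) |
| Both | 9 | soft tissue both improved and deteriorated, no other signs (3 × 3) |
| Stable | 4 | nothing improved, nothing deteriorated (2 × 2) |

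The total is 72, with none unclassified. The categories are exhaustive but not exclusive, and all 9 overlaps come from the soft-tissue row. These are counts of logical patterns, not patient frequencies.

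**Table against note.** Take a participant with class 3 already present at baseline, whose proptosis increases enough to raise the class 3 grade by one, whose class 2 signs fall one grade, and who shows no new class.

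- *Table 1:* the exophthalmos row has no deterioration criterion, no class has been added or increased, and the soft-tissue improvement criterion is met. Result: **Improved**.
- *Note:* one NOSPECS class has worsened by a grade. Result: **Deteriorated**.

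The two faults also interact. The NOSPECS deterioration criterion is printed in the soft-tissue row. If the note's rule is placed there, the worsening is in the same domain as the improvement, so it does not block Improvement, and the participant again carries both labels.

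**Possible size.** The documents give no frequency of mixed changes, so a fraction f of improvers, equal in both arms, is assumed to be moved to Deteriorated. The rates become 0.12(1 − f) and 0.37(1 − f). Exact power of the uncorrected Pearson test with 36 and 72:

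| f (assumed) | Control | HCQ | Power |
|---|---|---|---|
| 0 | 12.0% | 37.0% | 82.0% |
| 2% | 11.8% | 36.3% | 81.0% |
| 5% | 11.4% | 35.2% | 79.3% |
| 10% | 10.8% | 33.3% | 76.3% |

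**The case against.** The strongest reply is that the text can be read coherently. Deterioration is stated without exception, so its precedence is the natural reading. The note's two sentences have different scopes: the first concerns the soft-tissue domain, the second deterioration in general. A dash in the table can mean only that no separate millimetre criterion applies, with worsening captured through NOSPECS. The definitions are also said to follow the earlier selenium trial.

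This is a plausible guess at the intent, and it lowers the temperature. It does not remove the defect. Precedence has to be supplied by the reader against a phrase that limits the exclusion to the other domains. The benign reading of the dashes also requires the note to override a table cell that speaks of class rather than grade. The reference to the earlier trial does not reconcile table and note. Nor is this detail left to a fuller document, because the article prints the complete rule, and prints the three definitions twice.

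Several stronger readings are tempting but not supported:

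- *GO-QoL has the same double label.* The wording "An increase of 6 points in any category is considered improvement, a decrease of 6 points is considered deterioration" invites that inference, but Data collection and management {18a, 19} says that the two subscales are scored separately, and no combined GO-QoL class is defined.
- *Any chance one-line acuity drop cancels a real improvement.* The criterion is "Vision acuity deterioration or other evidence of optic nerve compression"; the word *other* suggests compression-related loss. The missing size of change is detail that an article may leave out, and the documents give no rate of chance drops.
- *The result is biased between arms.* Both arms use the same rule with blinded assessors, and the calculation above assumes equal attenuation.
- *Increases of 2 mm must be added as deterioration criteria.* That would be a debatable departure from the cited definition behind the 12% and 37% planning rates.

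**Conclusion.** The point holds in two parts. The Improvement and Deterioration categories overlap whenever the soft-tissue row meets both of its criteria, and no precedence is stated. Table 1 and its note also give different deterioration rules, so the same participant can be Improved under one and Deteriorated under the other. This is an ambiguity in the primary endpoint itself.

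Its numerical effect is unknown. With 5% or 10% of improvers reclassified equally in both arms, power would move from about 82% to about 79% or 76%. Those fractions are assumptions, and smaller ones do little (2% gives 81%). The conclusion that the rule is not unique rests on the printed text alone and does not depend on them.

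**What to change.** Before outcomes are examined by arm, amend Outcomes {12} and Table 1 as follows.

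1. State that Deterioration takes precedence. Deteriorated: any deterioration criterion in any domain. Improved: at least one improvement criterion and no deterioration criterion in any domain, including the one that improved. Stable: everyone else.
2. Use one NOSPECS deterioration wording in both the table and the note, settling class against grade. Say explicitly whether worsening eyelid aperture or proptosis counts and, if so, in which row. Choose the wording to match the cited definition from which the 12% and 37% planning rates were taken, so that endpoint and sample size stay aligned.

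The component measurements are already scheduled, so the cost is a text amendment with ethics review and a registry update where needed. The downside is that slightly fewer participants may count as improved, with some loss of power if mixed changes are common.
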